## **6.2 DATA MANAGEMENT SYSTEM**

Tayside Clinical Trials Unit (TCTU) will provide a data management system using OpenClinica (<https://www.openclinica.com/>), its standard GCP-compliant data management system. Case Report Forms (CRF) will be developed together with the trial management team, statistician and data manager to ensure that the data management system supports the research aims of the study. The data management

system will be fully validated, including the provision of test data and supporting documentation. Data entry will be coordinated by TCTU. Data will be stored on servers controlled through the Tayside Medical Science Centre and housed within the Health Informatics Centre and the University of Dundee. Backup and disaster recovery will be provided by TCTU according to its standard operating procedures. The Statistical Analysis Plan will specify dummy tables linked to primary and secondary outcomes and the data management system will be designed to export directly to the dummy table formats for analysis.

## **7 STATISTICS AND DATA ANALYSIS**

### **7.1 SAMPLE SIZE CALCULATION**

The rate of lung cancer is 187/100,000 per year for patients aged 50-74 in Scotland 2008 (ISD cancer statistics). Deprivation is associated with a higher risk of lung cancer. Those in the most deprived quintile are associated with an increased risk of 1.8 times compared to the middle quintile of deprivation. (ISD cancer statistics) this gives an estimated annual lung cancer rate of 336/100,000 among the practices taking part in the study. A high risk group within this population will be selected using similar entry criteria (outlined above) as the Mayo screening study which had a 2% prevalence rate of lung cancer and a further 2% incidence rate over the following 5 years (Swensson 2005). The baseline rate of late stage presentation for the particular high risk population envisaged in this study is uncertain, as is the size of the reduction in late stage presentation likely to be achieved through use of EarlyCDT-Lung. Using an estimated late stage presentation rate of 1,200/100,000 per year in the control group i.e. 2.4% over the two-year follow-up period, we require 85% power at 5% significance (two-sided) to detect an estimated reduction of 35% in presentation rate in the test group i.e. as low as 780/100,000 per year or 1.56% over the two-year follow-up period. This corresponds to an estimated event rate over the

two years of follow-up of 120 events in the control group and 78 events in the test group and implies a required sample size of  $n=5,000$  per group i.e. 10,000 altogether.

The anticipated 35% reduction in event rate between the control group and the test group is justified by current estimates of the capability of the EarlyCDT-Lung test to identify cases (41% sensitivity, 93% specificity) together with current estimates of the specificity of CT scanning (67%).

The sample size calculations are based upon standard methods for time to event data using the `cpower` function in R and `stpower` exponential procedure in Stata and assuming exponential survival. They were also confirmed using standard approaches for detecting a change in binomial probabilities, and confirmed using approaches to detect a change in Poisson rates (with essentially identical results as loss to follow up is expected to be low).

The study aims for a short recruitment period and so no allowance has been made for accrual. With such an allowance, say to 1 year, the power will increase to 91% to identify a 35% reduction provided the minimum follow up period of 2 years is observed.

For the follow-up analysis of behavioural and psychological outcomes, 200 participants in each group will allow a mean difference of 3.00 (SD 15.04 (unpublished data from the ProtecT prostate cancer study) in the Impact of Events Scale with 80% power and 2-sided 5% significance level. We will, however, collect data from 300 patients in each group to allow for attrition. Assuming 80% participants are current smokers, we will obtain 80% power at 5% significance level to detect a reduction in smoking from 80% to 67% i.e. 13% points difference assuming follow up on 200 participants.

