| Primary     | to assess the effectiveness of EarlyCDT-Lung test in reducing the incidence of patients with late-stage lung cancer at diagnosis, compared with standard clinical practice; | difference at 24 months after randomisation, between the number of patients with stage 3, 4 or unclassified lung cancer at diagnosis in the intervention arm, and those in the control arm;                                                                                                                                                                                                                                                                                                                                                                                                                                                                                                                                                                                                      |
| Secondary 1 | to assess the effectiveness of EarlyCDT-Lung test in improving the diagnosis of early-stage lung cancers;                                                                   | numbers, at 24 months after randomisation, in the different stages at diagnosis (3/ 4/ U/ other) in the intervention arm and the control arm;                                                                                                                                                                                                                                                                                                                                                                                                                                                                                                                                                                                                                                                    |

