## **OUTCOMES**

### *Primary*

The difference, at 24 months after randomisation, between the rates of patients with stage 3, 4 or unclassified lung cancer at diagnosis in the intervention arm, and those in the control arm;

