## **1.5 OUTCOMES**

### **1.5.1 Primary Outcomes**

The difference, at 24 months after randomisation, between the number of patients with stage 3, 4 or unclassified lung cancer at diagnosis in the intervention arm, and those in the control arm;

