## **7.2 PROPOSED ANALYSES**

Characteristics of participants will be compared informally between treatment arms at baseline. The main analysis of the primary outcome will be intention-to-treat. Cox proportional hazards models will be used to estimate the hazard ratio of the rate of late stage lung cancer in the intervention arm compared to the control arm.

Participants who are lost to follow up will be censored. The models will adjust for age, gender smoking history and practice. If appropriate, random cluster effects will be included rather than fixed effects for practices. A similar methodology will be used for the secondary outcomes of comparisons of mortality rates (secondary outcomes 3a and 3b). A subsequent analysis will compare the outcomes of those with EarlyCDT positive in comparison to those in the intervention group with EarlyCDT negative (primary contrast for this analysis) and those in the control group (secondary analysis 1). Comparisons of proportions (secondary analyses 1 and 4) will be carried out using chi square tests. Fishers exact test will be used if the numbers of events are small.

The analyses of the questionnaire responses (secondary analysis 5) will be carried out using the appropriate 2 sample t tests and regression methods at baseline. Non parametric tests will be used if there is evidence of non-normal scores. Multilevel models will be used to analyse the repeated scores during follow up.

Poisson regression models, adjusting for follow up time if necessary, will be used to investigate the other clinical measures (secondary outcomes 6 and 7).

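### The 91% power quoted for one year of accrual needs events after 24 months, which the primary outcome does not count; on the defined outcome power stays at about 85% (minor)

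*Protocol*

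**What the plan says.** The primary outcome has a fixed time point in three places. Section 1.5.1 gives "The difference, at 24 months after randomisation, between the number of patients with stage 3, 4 or unclassified lung cancer at diagnosis" in the two arms. The Summary has "The difference, at 24 months after randomisation, between the rates of patients with stage 3, 4 or unclassified lung cancer at diagnosis". The opening table of objectives and outcomes has "difference at 24 months after randomisation, between the number of patients with stage 3, 4 or unclassified lung cancer at diagnosis".

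The sample size in section 7.1 uses the same window. The control assumption is "Using an estimated late stage presentation rate of 1,200/100,000 per year in the control group i.e. 2.4% over the two-year follow-up period". The test-arm rate is "as low as 780/100,000 per year or 1.56% over the two-year follow-up period". This gives 120 and 78 expected events, 5,000 per group and 85% power at a two-sided 5% level. Exponential survival and low loss to follow-up are assumed.

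The same section then explains that accrual time was not allowed for, and adds: "With such an allowance, say to 1 year, the power will increase to 91% to identify a 35% reduction". It attaches the condition that everyone has at least two years of follow-up.

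**The concern.** The base calculation treats two years as the follow-up each person contributes. The accrual remark treats two years as the least that anyone contributes. These are different outcome windows, and only the first matches the primary outcome. If each participant is assessed at 24 months from their own randomisation, spreading entry over a year moves the calendar date of assessment but adds no person-time.

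What is at stake is how the figure is read. A funder, steering committee or monitoring committee could take it that slower recruitment raises power from 85% to 91%, that is, cuts the type II error from about 15% to 9%. Under the outcome as defined it does neither.

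**Working it through.** **Inputs (section 7.1).** 5,000 per group; hazards 0.012 and 0.0078 per year (ratio 0.65, ln 0.65 = −0.4308); two-sided 5% level (1.960); no loss to follow-up.

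**Power formulas**, with d1 and d2 events by arm and D = d1 + d2:
- Schoenfeld: Φ(√D/2 × 0.4308 − 1.960)
- Freedman: Φ(√D × 0.35/1.65 − 1.960)
- Log rate ratio: Φ(0.4308/√(1/d1 + 1/d2) − 1.960)

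**Step 1. The plan's 85%, outcome at 24 months.** Events: 5,000 × 0.024 = 120 and 5,000 × 0.0156 = 78, so D = 198.
- Schoenfeld: 14.07/2 × 0.4308 = 3.03, power 85.8%
- Freedman: 14.07 × 0.2121 = 2.98, power 84.7%
- Log rate ratio: 0.4308/0.1454 = 2.96, power 84.2%
- Two proportions, 2.4% v 1.56%: power 85.4% (85% needs 4,938 per arm)

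The stated 85% reproduces.

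**Step 2. The plan's 91%, one year of accrual with open follow-up.** Assume uniform entry over one year and a common closing date two years after the last entry, so that follow-up runs from 2 to 3 years (mean 2.5). The event probability per person is 1 − [exp(−2λ) − exp(−3λ)]/λ.
- Control, λ = 0.012: 2.955%, or 147.7 events
- Test, λ = 0.0078: 1.931%, or 96.5 events
- D is about 244

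Results:
- Schoenfeld: 15.63/2 × 0.4308 = 3.37, power 92.0%
- Freedman: 15.63 × 0.2121 = 3.32, power 91.2%
- Log rate ratio: 0.4308/0.1309 = 3.29, power 90.9%

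Two variants give much the same. Hazards derived from 2.4% over two years give about 247 events and 91.2% to 92.3%. Rate times mean follow-up gives 5,000 × 0.012 × 2.5 = 150 and 150 × 0.65 = 97.5, total 247.5, with log rate ratio 3.31 and power 91.2%.

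The stated 91% reproduces, but only on this window.

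**Step 3. One year of accrual with the defined outcome.** Each person contributes at most 24 months, so the events are again 120 and 78 and power is as in step 1.

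| | Outcome at 24 months | All follow-up, 2 to 3 years |
|---|---|---|
| Expected events | 198 | 244 to 248 |
| Power for a 35% reduction | 84.2% to 85.8% | 90.9% to 92.3% |

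The gain therefore depends on about 46 to 50 events (244 − 198 to 248 − 198) that the primary outcome does not count. With the window held at 24 months, 91% would need about 235 (Schoenfeld) to 243 (Freedman) events, or 5,992 per arm by the two-proportion formula.

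**The case against.** The best defence is that the remark is conditional and states its premise. Calling two years a minimum signals follow-up to a common closing date, which suits the time-to-event methods of section 7.1 and the Cox model of section 7.2. Under that premise the figure is right. The remark is also an aside: the adopted design power is 85%, with no accrual allowance. All of this stands and is why the point is minor. It does not remove the inconsistency, because the premise is not the window in which the primary outcome is defined.

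A reader might go further and infer that section 7.2 is defective, because it says "Participants who are lost to follow up will be censored" and gives no cut-off at 24 months. The documents do not support that. The sentence does not say that loss to follow-up is the only ground for censoring, and administrative censoring is commonly left to a statistical analysis plan. Section 6.2 foresees such a plan, and it is not shown here.

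A reader might also argue that events after 24 months fall after screening CT has ended, so the effect must fade. The imaging schedule does not bear this out. The last CT is at 24 months with a window of plus or minus 4 weeks. Imaging starts only after a test result that may come up to 4 weeks after the randomisation visit. The final scan and diagnoses from it can therefore fall later than 24 months from randomisation.

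**Conclusion.** The point holds as an inconsistency between the accrual remark in section 7.1 and the primary outcome. On the defined outcome, power for a 35% reduction is about 85% whatever the accrual period, not 91%. The 6-point gain belongs to an analysis that counts events over 2 to 3 years of follow-up.

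Two stronger readings are tempting and do not hold. The 91% is not a miscalculation, since it reproduces for the longer window. Nor is the trial smaller than its stated design requires: 5,000 per group rests on the 85% calculation, which stands.

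The open follow-up figures assume uniform entry over one year, constant hazards, negligible loss to follow-up, and a 35% reduction that continues unchanged beyond 24 months. The protocol gives no separate support for that last assumption. The conclusion for the 24-month outcome does not depend on the entry pattern or on what happens after 24 months.

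**What to change.** In section 7.1, delete the 91% sentence, or replace it with a statement that power is about 85% for a 35% reduction whatever the accrual period, because each participant's primary outcome is assessed at 24 months.

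If the sponsor wants to keep the 91%, attach it to an explicitly labelled supplementary analysis of all follow-up to a common closing date, and state the assumption that the 35% reduction persists beyond 24 months.

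The cost is one sentence and one less favourable figure. The sample size, the outcome definition and the planned model stay as they are.

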| 5           | to assess behavioural outcomes including smoking, psychological outcomes including cancer worry, anxiety, depression, distress specific to clinical investigations;         | scores at baseline, and follow-up on EQ5D, Hospital Anxiety and Depression Scale (HADS), Positive and Negative Affect Schedule (PANAS), Revised Illness Perception Questionnaire – Lung Cancer (IPQ-LC), Lung cancer risk perception, Health anxiety subscale of Health Orientation Scale (HOS) and the Lung Cancer Worry Scale (LCWS), Medication, smoking behaviour, demographic details. Follow-up questionnaires include same items, plus Impact of Events Scale (intervention group only), healthcare utilisation and dates and results of follow-up investigations for lung cancer (test positive group only). The HADS is not included in follow-up questionnaires. Follow-up questionnaires are administered between 1 and 24 months to subsets of the control arm and intervention arm; |

|          |                                                                                                                                                                                  |                                                                                                                                                                                                                                                                                                                                                           |
|----------|----------------------------------------------------------------------------------------------------------------------------------------------------------------------------------|-----------------------------------------------------------------------------------------------------------------------------------------------------------------------------------------------------------------------------------------------------------------------------------------------------------------------------------------------------------|

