## **6 DATA COLLECTION & MANAGEMENT**

### **6.1 DATA COLLECTION**

It is the CI and PIs responsibility to ensure the accuracy of all data entered and recorded in the CRF/eCRFs and the database. The Delegation of Responsibilities Log will identify all trial personnel responsible for data collection, entry, handling and managing the database.

The data will be collected by the RN and/or the PI either directly onto a paper CRF with subsequent transcription to the eCRF, or direct data entry onto the web based eCRF. Where there is electronic storage of non-identifiable data this will be on a password protected device and/or database. A plan for data quality control will be developed by the data management staff at Tayside Clinical Trials Unit and the trial management team.

All research blood samples (anonymised using barcodes) will be labelled and packaged according to IATA regulations using Royal Mail Safeboxes or INTELSIUS or equivalent transport box systems to be transported to the University of Nottingham for processing, transporting and storage of samples for future research. All samples will be stored under custodianship as per UK Biobank guidelines. Sample Analysis and Chain of Custody Plans will be documented in the Study Operations Manual. The participant's medical notes (GP and hospital) paper or electronic will act as source data for relevant past medical history, subsequent medical conditions, hospital admissions and diagnostic reports.

Psychological and behavioural data relating to smoking, psychological outcomes including cancer worry, anxiety, depression and distress will be collected on all 10,000 participants through a baseline questionnaire administered during Visit 1. If required the RN can assist the participant with the completion of the questionnaire. Follow-up data will be collected between 1 and 24 months on subsets of the intervention and control groups. All participants in the EarlyCDT-positive group will be approached with the recruitment aim of 300 from this group collected at 1,3,6,12,18 and 24 months. The EarlyCDT-negative and control groups will be approached at the same rate as the EarlyCDT-positive group with the recruitment aim of 300 from each group, collected at 1,3,6 and 12 months.. A web-based tool will be used weekly to randomly sample patients from the EarlyCDT-negative and control groups, stratified by the two study centres. It is anticipated an average of 8 individuals (4 from each of

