the two study centres) will be randomly sampled and invited to complete follow-up questionnaires from each of the EarlyCDT-negative and control groups per week (based on a 10 month recruitment period and an anticipated response rate of 67%). Response rates will be monitored and if they are lower than 67%, the number randomly sampled at each centre will be increased to achieve a minimum of 200 responses. Participants will be sent a £5 gift voucher for use in a range of stores for each questionnaire to be completed. A Cochrane review found the use of small monetary incentives significantly increases response rates to postal questionnaires (Edwards et al., 2009). There are precedents in trials and other UK studies where small monetary incentives have been used.

Two methods will be used for the initial period of recruitment: 50% of the sample will receive the questionnaire with the voucher and 50% will receive the voucher once they have returned their questionnaire. An assessment will be carried out to determine which of the two methods is more effective in maximising recruitment rate and will then be employed for the remainder of the study. .

A phone number will be provided for participants to call the research team for assistance in completing questionnaires. Occasionally the research team may call participants to check on postal delivery and offer assistance with completion to increase return rate. Participants who develop lung cancer during the 24 month follow-up period will not be sent further study questionnaires.

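### The Impact of Events Scale power statement in section 7.1 cannot be reproduced: two groups of 200 give about 51% power for a 3-point difference, not 80%

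*Protocol*

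**What the plan says.** Protocol section 7.1 justifies the size of the psychological follow-up sample with one sentence: "200 participants in each group will allow a mean difference of 3.00 (SD 15.04", followed (after the source of the SD) by "in the Impact of Events Scale with 80% power and 2-sided 5% significance level". It adds that the trial will "collect data from 300 patients in each group to allow for attrition". It mentions no pairing, baseline adjustment, number of visits or within-person correlation.

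The opening objectives and outcomes table fixes who receives the scale: "Follow-up questionnaires include same items, plus Impact of Events Scale (intervention group only"). The Summary and section 1.5.2 repeat this. There is therefore no baseline score and no score in the control arm.

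Section 7.2 plans "appropriate 2 sample t tests and regression methods at baseline" for the questionnaires, and multilevel models for the repeated follow-up scores.

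Section 6.1 sets the sampling of the test-negative and control groups "with the recruitment aim of 300 from each group, collected at 1,3,6 and 12 months". On the weekly draw it says "It is anticipated an average of 8 individuals (4 from each of" the two centres), for each of those groups, based on ten months of recruitment and a 67% response rate. If response is lower, "the number randomly sampled at each centre will be increased to achieve a minimum of 200 responses".

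**The concern.** The wording describes two groups of 200, but the figure does not behave like a two-group calculation. A difference of 3.00 against an SD of 15.04 is a standardised effect of about 0.2, and 200 per group is well short of what 80% power normally needs for an effect of that size.

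The scale measures distress linked to the test and its follow-up. If the stated power is wrong, a reader of a null result would believe that a 3-point difference had been sought with 80% power when the chance of finding it at a given visit was nearer one half. The figure of 200 also reappears in section 6.1 as the minimum number of responses, so it affects conduct as well as text.

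**Working it through.** **Inputs (protocol).** Difference 3.00, SD 15.04, 200 per group, two-sided 5%, 80% power, 300 per group collected (7.1). Scale at follow-up only, intervention arm only (outcomes table, Summary, 1.5.2). Shared visits at 1, 3, 6 and 12 months; eight invitations per group per week; 67% response; ten months (6.1). Forty-eight working weeks a year (2.3), so ten months is 40 weeks. Expected positives 400-450 (Summary, 4.7).

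**1. Trying to reproduce the 80%.**

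- Two independent means: SE = 15.04 × √(2/200) = 1.504. Ratio = 3/1.504 = 1.995. Power = Φ(1.995 − 1.960) = 51.4% (noncentral t: 51.2%).
- One-sided 5%: 63.7%.
- One-sample or paired: SE = 15.04/√200 = 1.063, ratio 2.821, power 80.5% (t: 80.2%). Solving for n gives (15.04 × 2.802/3)² = 197.3, or 199.2 with the t distribution, which rounds up to 200.

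Of the variants tried, only the one-sample or paired form returns the stated figure.

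**2. What 80% would need with two groups.** n = 2 × 197.3 = 394.5, so 395 per group (t: 396). At the protocol's own ratio of 200 retained from 300, that is 395 × 1.5, about 593 recruited per group, against 400-450 expected positives. Alternatively, the SD would have to be 10.71 instead of 15.04.

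**3. What the planned numbers detect at one time point.**

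| Completers per group | Power for 3.00 | Difference detectable at 80% |
|---|---|---|
| 200 | 51% | 2.802 × 1.504 = 4.21 |
| 300 (no attrition) | 68% | 2.802 × 1.228 = 3.44 |

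**4. Possible gain from repeated measures.** Assume the target is the mean of four visits, complete data and an equal correlation ρ between visits. The variance is then multiplied by (1 + 3ρ)/4. Reaching 80% with 200 per group needs a factor of 0.507, so ρ = (4 × 0.507 − 1)/3 = 0.34. At ρ = 0.5 the factor is 0.625 and power is 71%. At ρ = 0.7 it is 0.775 and power is 62%. The protocol gives no ρ; this range is an assumption.

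**5. The number 300.** 8 × 40 = 320 approached per group, and 320 × 0.67 = 214 responders. For comparison, 300 × 0.67 = 201.

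**6. A check on the same paragraph.** The smoking statement (80% against 67%), read as 200 per group, gives 84% power, with 180 per group needed (195 with continuity correction). It holds as a two-group calculation, so the problem is confined to the Impact of Events sentence.

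**The case against.** The strongest defence is the multilevel model in section 7.2. Repeated scores carry more information than one score, so 51% is not the power of the planned analysis, and a reader who concludes that the trial would miss a 3-point difference half the time goes too far. This stands in part: 51% applies to a single time point. It does not support the 80%, because section 7.1 describes one mean difference and gives no correlation, and only a correlation of about 0.34 or lower would reach that figure. Baseline adjustment cannot help, since the scale is not collected at baseline.

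A reader might infer that a one-sample formula was used by mistake. The match is close, but the protocol names no formula for this calculation, so that remains an inference. The power shortfall does not depend on it.

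A reader might also infer that the weekly draw was miscalculated, since it yields 214 and not 300. The text does not establish that. About 300 approached and at least 200 responding is a coherent plan, and it agrees with both the 67% response rate and the minimum of 200. What conflicts is the wording: section 7.1 speaks of collecting data from 300, and section 6.1 of a recruitment aim of 300.

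Finally, this is one scale among several. The positive and negative affect, lung cancer worry, health anxiety and risk perception measures are also followed up, including in controls. Nothing in the protocol makes this scale the main evidence on distress.

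**Conclusion.** The stated 80% is wrong as written for a comparison of two independent groups at one time point: the protocol's own inputs give about 51%, a shortfall of about 29 percentage points. A true 80% needs about 395 completers per group, or a target difference of about 4.2 points with 200. This rests on the stated SD and on the contrast being test-positive against test-negative, which follows from who receives the scale. Under the planned repeated-measures model the power may be higher, but the amount cannot be judged without a stated correlation.

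The meaning of 300 per group is a separate ambiguity, and no error in the draw is shown. The point should be fixed, but it concerns a secondary outcome and leaves the primary sample size untouched.

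**What to change.** 1. **Section 7.1.** Replace the sentence with what the design supports: 200 completers per group detect about 4.2 points with 80% power at two-sided 5%, and have about 51% power for 3.0 points. If 300 complete with no attrition, the figures are about 3.4 points and 68%.
2. **Or**, if the power is meant to rest on the multilevel model, say so and state the number of visits, the within-person correlation and its source. With four visits, 80% requires about 0.34 or lower, and 0.5 gives about 71%.
3. **Sections 6.1 and 7.1.** State whether 300 per group means people approached or responders. If approached, the draw of eight a week and the minimum of 200 can stay, and the wording about collecting data from 300 should change. If responders, the draw needs about 300/0.67/40 = 11.2 a week per group, and the minimum should be aligned with 300.

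Enlarging only the test-negative sample does not rescue the 3-point target. A draw of 300 against 600 would give about 80% only if everyone completed. At the planned retention of 200 from 300 it becomes 200 against 400, or 63%. Even 200 positives against all of the roughly 4,600 negatives (5,000 less 400-450) reach only about 79%.

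Items 1 and 2 cost wording only. Under the responder reading, item 3 adds 300 − 214 = 86 responders per sampled group, or 86 × 4 × £5 = £1,720 in vouchers per group, before postage and any vouchers sent to people who do not reply. No further trial participants are needed.
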